Whether surgeons do or do not obliterate the mastoid cavity after CWU tympanomastoidectomy today, seems to depend mostly on their personal experience, preferences, and scientific beliefs. Within the present ENT community, the usefulness of the obliteration is still widely discussed and is still a topic of current interest in literature, during congresses and within ENT-societies. The superiority of the technique is merely explored retrospectively in the literature with several confounding factors and a high risk of bias (such as difference in but not limited to; patient-related factors, surgical technique; obliteration material; follow-up periods; exclusion/inclusion criteria). Furthermore, current research rarely categorizes outcomes based on cholesteatoma extension and localisation, as for example classified using the STAMCO stages (18).

In addition to recidivism of cholesteatoma, hearing is another important outcome measure. In the literature, most research is conducted on hearing outcomes after CWD or canal wall reconstruction surgery with mastoid and epitympanic obliteration. Numerous studies show that these two similar techniques preserve preoperative hearing outcomes, or even moderately improve it (19–23). However, there is limited literature available on hearing outcomes following CWU with obliteration. The few retrospective studies that have recently been carried out show promising results that this approach also ensures hearing preservation (24–26). When using the obliteration technique in the epitympanum (a part of the middle ear), a part of the ossicular chain (part of the malleus and incus) must be removed, which poses a risk for hearing loss after surgery. It is therefore useful to investigate the relation between CWU tympanomastoidectomy with obliteration and hearing outcomes to either confirm or deny the retrospective evidence that recurrence and residual rates are lower due to the obliteration.

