All pre-operative measurements are part of standard care in the Netherlands and Belgium. Pre-operatively patients receive an audiometric exam, a physical examination of the ear, a CT-scan and fill in the patient-reported outcome measure (PROM). Follow-up will be planned at least at 6-18 weeks, at around 1 year and at around 3 years after surgery. It is important to note that conducting a CT scan and audiometry preoperatively as well as the DW-MRI's after 1 and 3 years are part of the standard care. In line with standard care, if there is a suspicion for recurrent or residual pathology (either clinically by micro-otoscopy or radiologically by DW-MRI) the treating physician will perform a revision surgery. If during revision surgery the suspicion is confirmed, the type of recidivism (residual or recurrent) is recorded and the follow-up of the patient ends. Data that is collected up until the point of detection of residual or recurrent disease will be used for analysis (this is not an exclusion criterium). If the suspicion is not confirmed (false-positive) then the patient will continue the follow-up as planned (unless a reconstructive procedure with the goal of improving hearing has been performed). During the three years of follow-up, patients should not undergo another type of ear surgery. If this is unavoidable, as judged by the treating physicians, the patient will be retrospectively excluded. In order to ensure that the same surgical data is collected in all participating centers, a standardized operation report will be written and shared by the sponsor (UMC Utrecht). This operation report will be recorded in the electronic patient dossier (with the exception of the information if obliteration was used or not) and transferred to Castor EDC. In Castor there will be a variable to also record if obliteration has taken place or not. The only methodology that is different to standard care is the randomization of the patients and the completion of the questionnaire. It is important to note that the technique used for the obliteration technique differs slightly between centers. The exact surgical technique will be described by the participating otologists and included in the description of the study, for example in a publication.

**Figure 1.** Flowchart of the study. *Standard care is indicated by \**[figure not shown]

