## 6.2 Randomisation, blinding and treatment allocation

If they sign the informed consent form they will be randomly allocated to one of the two treatment groups (A or B) using the Randomization Tool in Castor. Patients will be randomly assigned to one of the two study groups (A or B). A website randomisation program built within Castor will be used for the randomization. After informed consent, patients will be randomized. This is a single blind study, meaning that only participants are blinded for the treatment allocation. The surgeons cannot be blinded, as they will know which procedure they performed. The surgeon will not write down which procedure the patient received in the surgical report or in the letter to the general practitioner. It will only be recorded in Castor and in the RFS map. De blinding (single-sided) will only be lifted if it is in the interest of the safety of the participant. De participant and/or general practitioner can request this from the treating physician (ENT-surgeon) who performed the surgery. The ENT-surgeon will decide if lifting of the blinding is necessary and inform the researcher about this event. Only in case of medical emergency and in absence of the treating physician, other medical specialists can lift the blinding by checking the placement of the patient in the RFS map. All medical specialists have access to the RFS map with information of the participants where an inclusion table with randomization is stored. This way it is possible to lift blinding 24 hours a day.

Stratification will be used to distribute the two groups as evenly as possible between the participating centres. Patients are randomized into one of two groups in an equal 1:1 allocation ratio. A 4,6,8 block randomization will be used.

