#### **6.5 Replacement of individual subjects after withdrawal**

See also section 4.4 sample size calculation. To anticipate possible withdrawal a 10% margin is taken into account to still provide sufficient power (of 0.80). An intention to treat analysis will be used, there is no reason to replace patients after withdrawal.

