## **Economic evaluation**

- A cost utility analysis will be performed as described under the methods section.

The amount of missing data will be mentioned in the results. Missing data will be imputed using multiple imputation. All analyses will be performed on an intention-to-treat basis.

Additionally, dropout rates will be monitored, and any differential attrition between treatment arms will be appropriately accounted for in the statistical analysis.

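### Retrospective exclusion of randomised patients who need other ear surgery contradicts the intention-to-treat analysis and can bias the primary comparison in either direction

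*Protocol*

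**What the plan says.** Section 3 (Study design) sets the rule in two sentences: "During the three years of follow-up, patients should not undergo another type of ear surgery", and then "If this is unavoidable, as judged by the treating physicians, the patient will be retrospectively excluded". What counts as another type of ear surgery is not defined.

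Section 6.5 says: "An intention to treat analysis will be used, there is no reason to replace patients after withdrawal". The closing paragraphs of section 8.2, placed under the economic evaluation, say: "All analyses will be performed on an intention-to-treat basis".

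Section 3 treats two neighbouring situations differently:

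- **Confirmed recidivism at revision surgery.** Follow-up ends, but the data stay in: "Data that is collected up until the point of detection of residual or recurrent disease will be used for analysis (this is not an exclusion" criterion).
- **Revision surgery that does not confirm the suspicion.** The patient continues follow-up, "unless a reconstructive procedure with the goal of improving hearing has been performed".

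On who judges, section 6.2 states: "The surgeons cannot be blinded, as they will know which procedure they performed". Section 3 identifies the treating physician as the ENT surgeon who did the operation.

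**The concern.** The rule takes a patient out of the trial because of something that happens after randomisation. The decision that triggers it is made by someone who knows the arm. The need for later ear surgery could differ between arms. Section 1 says that with epitympanic obliteration "a part of the ossicular chain (part of the malleus and incus) must be removed, which poses a risk for hearing loss after surgery", which gives one possible route to later hearing surgery in the obliteration arm, although the protocol does not itself draw that link.

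If exclusion depends on the arm and the excluded patients differ from the others in their risk of recidivism, the remaining groups are no longer comparable and the primary result carries a bias that no later analysis of the retained patients can remove. The analysis population for the primary endpoint is also undefined for these patients, because two parts of the protocol give opposite instructions.

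**Working it through.** **1. The passages side by side.**

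| Place | Situation | What happens to the data |
|---|---|---|
| Section 3 | Other ear surgery judged unavoidable, within three years | Patient excluded retrospectively |
| Section 3 | Confirmed recidivism | Data up to detection used; not an exclusion |
| Section 9.2 | Patient stops participation | Data kept, because deletion would bias the database |
| Sections 6.5 and 8.2 | All randomised patients | Intention-to-treat |

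Row 1 cannot hold together with row 4, and it runs against the reasoning of row 3. Row 2 shows that the authors do distinguish stopping follow-up from excluding, so the exclusion cannot simply be read as censoring. Nothing in the protocol limits it to a per-protocol set or to the hearing analysis.

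**2. The plan's own figure.** Section 4.4: 20% v 40%, two-sided alpha 0.05, pooled Z test, 80 per arm, stated power 0.8009 and actual alpha 0.0472. Exact binomial enumeration gives power 0.8009, and type I error 0.0472 at a common rate of 40%. The 10% margin gives 160/0.90 = 177.8, so 178. The sample size is not in question.

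**3. Bias from exclusion.** Let p be the true recidivism rate in an arm, e the fraction excluded and q the recidivism rate among the excluded. The rate among those kept is

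(p − e·q)/(1 − e) = p + (p − q)·e/(1 − e).

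The protocol gives neither e nor q. Assume p = 0.30 in both arms (no true effect), e = 0.05 without obliteration and e = 0.15 with it. Then e/(1 − e) is 0.0526 and 0.1765, a difference of 0.1238, and the spurious difference (obliteration minus no obliteration) is (0.30 − q) × 0.1238. Type I error is by exact enumeration at 80 × 0.95 = 76 and 80 × 0.85 = 68 patients.

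| q (assumed) | No obliteration | Obliteration | Spurious difference | Type I error |
|---|---|---|---|---|
| 0% | 31.6% | 35.3% | +3.7 points | 0.074 |
| 10% | 31.1% | 33.5% | +2.5 points | 0.060 |
| 30% | 30.0% | 30.0% | 0 | 0.049 |
| 50% | 28.9% | 26.5% | −2.5 points | 0.062 |
| 60% | 28.4% | 24.7% | −3.7 points | 0.079 |

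For example, at q = 50%: (0.30 − 0.05 × 0.5)/0.95 = 0.289 and (0.30 − 0.15 × 0.5)/0.85 = 0.265. Swapping the two exclusion rates reverses every sign. With equal exclusion fractions and the same q in both arms, the difference under no effect is zero.

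**4. Loss of numbers.** If exclusions unrelated to risk removed a further 10% beyond the planned margin, 72 per arm would remain and exact power would be 0.757. That 10% is also an assumption.

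**5. Time window.** The exclusion rule speaks of three years. Sections 6.1.1 and 8.1 take the primary endpoint to 60 months, so other ear surgery in years 3 to 5 is not addressed.

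**The case against.** Several points on the other side stand.

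- **Who excludes.** A reader might infer that unblinded physicians choose whom to exclude. They judge only whether the surgery is unavoidable; exclusion then follows from the rule. Knowledge of the arm enters through that trigger.
- **The follow-up stop after a negative revision with hearing reconstruction.** It is tempting to call this a second breach of intention-to-treat. It is not: the patient is not excluded, the data so far are not discarded, and later outcomes are simply missing. It remains a weakness, because later recidivism status is lost after an event that may depend on the arm.
- **Dependence on arm.** Section 1 ties epitympanic obliteration to a risk of hearing loss, not to later surgery, and also reports retrospective studies that suggest hearing is preserved. The text supports that the need for surgery could depend on the arm, not that it probably does.
- **Hearing.** One might infer that hearing is the outcome most affected. Other ear surgery is not equated with hearing reconstruction anywhere, and audiometry ends at about one year (Table 1), so the documents do not show this.
- **Size and direction.** Every exclusion rate and risk above is assumed. Because confirmed recidivism stays in the analysis, a high recidivism rate among the excluded is not the obvious case, and a low one biases the other way.

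The protocol also plans multiple imputation (section 8.1) and promises to account for differential attrition (section 8.2). These bear on missing outcomes. They do not rescue the exclusion rule, because a patient removed by rule is outside the analysis set rather than missing within it. If imputation is intended for these patients, the protocol has to say so.

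**Conclusion.** The sentence in section 3 is wrong as written: it contradicts the intention-to-treat analysis in sections 6.5 and 8.2 and the reasoning of section 9.2. This rests on the text alone.

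The consequence is that the primary comparison can be biased, in a direction that cannot be known in advance. Under the assumed 30% recidivism and 5% v 15% exclusion, the spurious difference is about 2.5 to 3.7 points either way, with type I error of about 0.06 to 0.08 instead of 0.049. That is small beside the 20-point difference the trial is designed to detect, and it vanishes if exclusions are few, balanced and unrelated to risk. The protocol does nothing to ensure those conditions. The documents do not support a claim that bias will occur, or that it will favour obliteration.

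**What to change.** In section 3, replace the retrospective exclusion with wording to this effect:

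- Every randomised patient stays in the primary analysis in the allocated arm.
- All data collected up to the other ear surgery are used.
- That surgery is recorded with its date as an intercurrent event.
- Later outcomes follow a stated rule: used if observed, otherwise handled by the multiple imputation already planned in section 8.1. The same rule should cover patients whose follow-up stops after a negative revision with hearing reconstruction.
- The rule applies over the full 60 months of the primary endpoint, not three years only.
- Any exclusion is confined to a per-protocol or sensitivity analysis.

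How hearing values after such surgery enter the hearing analysis is a choice of estimand that the statistical analysis plan can settle; this point does not prescribe it.

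The cost is a change of wording. The sample size stays at 178 and clinical management is untouched. The small downside is that some outcomes will reflect a later operation.

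### Section 3 retrospectively excludes randomised patients who have another type of ear surgery within three years, which contradicts the intention-to-treat analysis promised in Sections 6.5 and 8.2

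*Protocol*

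**What the plan says.** Protocol Section 3 (Study design) sets the rule in two sentences: "During the three years of follow-up, patients should not undergo another type of ear surgery", and then "If this is unavoidable, as judged by the treating physicians, the patient will be retrospectively excluded". It limits the exclusion to no endpoint or time point, and it does not say that data collected before the other surgery are kept.

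The same section treats revision surgery for suspected recidivism differently:

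- If recidivism is confirmed, follow-up ends, but the data up to detection "will be used for analysis (this is not an exclusion criterium").
- If it is not confirmed: "If the suspicion is not confirmed (false-positive) then the patient will continue the follow-up as planned". An exception in brackets follows for patients who had a hearing reconstruction. Their status in the analysis is not stated.

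On who knows the arm, Section 6.2 says: "The surgeons cannot be blinded, as they will know which procedure they performed".

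On the analysis set, Section 6.5 says: "An intention to treat analysis will be used, there is no reason to replace patients after withdrawal". Section 8.2, in the closing text under the economic evaluation, says: "All analyses will be performed on an intention-to-treat basis".

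Section 9.2 adds that data already collected from a patient who stops participation are kept, because deleting them would bias the database significantly.

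**The concern.** The rule removes a randomised patient because of something that happens after randomisation. The step that triggers it, judging that another operation is unavoidable, is taken by physicians who know the arm, and no blinded adjudication is provided. Randomisation protects the comparison only while all randomised patients are analysed in their arm.

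Later ear surgery could plausibly depend on the technique. Section 1 says that for epitympanic obliteration "a part of the ossicular chain (part of the malleus and incus) must be removed, which poses a risk for hearing loss after surgery", and a patient with poor hearing is one who might later have a hearing operation. If such patients leave the data set, those with the worse course are missing from the hearing, OQUA and cost comparisons. If their recidivism risk differs from that of the other patients in their arm, the primary comparison shifts too.

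At stake are the validity of the primary comparison, the completeness of the secondary comparisons, and some of the planned power.

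**Working it through.** **1. Can the two rules be reconciled from the text?** Three readings would remove the conflict.

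- *Excluded means only that follow-up stops.* A few sentences earlier, Section 3 describes exactly that for confirmed recidivism: follow-up ends, the data are used, and this is said not to be an exclusion. The authors separate the two ideas and chose exclusion for other ear surgery.
- *The missing-data provisions restore these patients.* Section 8.1 imputes missing outcomes. Section 8.2 says that differential attrition will be accounted for. Neither says that a retrospectively excluded patient stays in the analysis set.
- *The protocol accepts removal of data in general.* Section 9.2 says the opposite for patients who stop.

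None works, so the contradiction stands on the text alone and needs no arithmetic.

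**2. The plan's own figure.** Inputs from Section 4.4: 80 per arm, 40% (control, group A) against 20% (treatment, group B), two-sided pooled Z test, alpha 0.05. Exact enumeration over both binomial distributions gives power 0.8009 and, at 40% in both arms, actual alpha 0.0472. Both match the printed table. The total also reproduces: 160 / 0.90 = 177.8, rounded up to 178.

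**3. Exclusion unrelated to outcome.** The excluded share e is an assumption. It is taken on top of the 10% margin.

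| e | n per arm | exact power (40% v 20%) |
|---|---|---|
| 0 | 80 | 0.801 |
| 5% | 80 × 0.95 = 76 | 0.775 |
| 10% | 80 × 0.90 = 72 | 0.757 |

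There is no bias in this case.

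**4. Exclusion related to arm and outcome.** Let p be the true recidivism risk in an arm and r the risk among its excluded patients. The rate among those left is (p − e·r) / (1 − e). Assume r = 60% in A and 10% in B, values chosen only for illustration.

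*No true effect, p = 30% in both arms:*

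- e = 5%: A (0.30 − 0.05 × 0.60) / 0.95 = 28.4%; B (0.30 − 0.05 × 0.10) / 0.95 = 31.1%. At 76 per arm the test rejects with probability 6.4%, against 4.9% with no bias.
- e = 10%: A (0.30 − 0.10 × 0.60) / 0.90 = 26.7%; B (0.30 − 0.10 × 0.10) / 0.90 = 32.2%. At 72 per arm it rejects with probability 11%, against 5.1% with no bias.

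*True effect 40% v 20%:*

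- e = 5%: A 0.37 / 0.95 = 38.9%; B 0.195 / 0.95 = 20.5%; power 0.71.
- e = 10%: A 0.34 / 0.90 = 37.8%; B 0.19 / 0.90 = 21.1%; difference −16.7 points; power 0.60.
- e = 10% with the risks swapped (10% in A, 60% in B): A 0.39 / 0.90 = 43.3%; B 0.14 / 0.90 = 15.6%; difference −27.8 points.

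The direction depends on which assumption is made, and the documents do not settle it.

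**The case against.** The strongest reply is that the rule is narrower than it looks and that its effect is unknown. Several parts of this stand.

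- A reader might infer that any further ear operation excludes. The text says another type of ear surgery, directly after it has dealt with revision for suspected recidivism. That pathway is not in itself an exclusion.
- A reader might infer that group A loses patients operated on for retraction without cholesteatoma. The Summary records retraction as suspicion of recidivism, and Section 3 sends suspicion to revision surgery. That mechanism is therefore not supported.
- A reader might infer that contralateral surgery excludes. The text names no side. This is a silence, not a stated trigger.
- A reader might infer that later hearing surgery will be more common in group B. Section 1 names the hearing risk, but it also cites retrospective studies that suggest preserved hearing. Dependence on arm is possible, not shown.
- The 10% margin is for dropouts, a term the protocol does not define. It might already cover these patients, and then the power loss in step 3 would not arise.
- The bias figures need an assumed share and opposed, extreme risks. At 5% excluded the false-positive rate barely moves.

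What does not stand is the idea that the conflict can be left to the SAP. The protocol itself states both rules, and no analysis set satisfies both once a single patient is excluded.

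**Conclusion.** The contradiction is established by the text: Section 3 removes randomised patients for a post-randomisation event judged by physicians who know the arm, and Sections 6.5 and 8.2 promise intention-to-treat. It should be resolved before any patient is excluded, because the rule decides who enters the primary analysis and every other comparison.

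Bias is a possibility whose size the documents cannot give. It arises only if exclusion is related to outcome in a way that differs between arms, or if its frequency differs between arms and it is related to outcome. With exclusions unrelated to outcome, the cost is at most the power loss shown, and only if they fall outside the dropout margin. The figures for 5% and 10% excluded illustrate what could happen. They do not support a claim that the trial's result will be biased, or in which direction.

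A lesser wording gap belongs with this: the rule speaks of three years, whereas Sections 6.1.1 and 8.1 run the primary endpoint to five.

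**What to change.** - Replace the retrospective exclusion in Section 3 with a statement that every randomised patient stays in the analysis set of the allocated arm, whatever later ear surgery occurs.
- Record the type, side and date of any other ear surgery in Castor, and continue the scheduled outcome collection.
- Use the data regardless of that surgery for the primary, quality-of-life and cost analyses. Add a sensitivity analysis that sets aside data after other surgery on the same ear.
- State that patients with a false-positive revision plus hearing reconstruction remain in the analysis set.
- Reconcile the three-year wording with the five-year endpoint.

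Whether and when other ear surgery is done is clinical management and is not addressed here.

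The cost is a short protocol amendment and a small addition to the Castor form, with no extra patients or visits. The planned 178 patients and the exact power of 0.801 at 80 per arm stay as they are. The downside is that hearing and OQUA values will include the effect of some later surgery.
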